### Sequence generation {16a}

An investigator not overseeing the in-lab sessions will construct the randomization sequence for each participant using the SAS statistical software procedure PROC PLAN (Cary, NC). The sequences will adhere to the Williams design [91], which ensures a uniform crossover design with a balance of order in the experiment as a whole.

### Concealment mechanism {16b}

The assignment for each participant visit will be transferred to sealed opaque envelopes to be opened at the beginning of each session.

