### Trial design {8}

We will use a randomized crossover trial study design with three study arms/conditions. All three conditions will involve continuous monitoring over 72 h and will begin with a 36-h at-home period, followed by 24 total hours in the lab (including a 12-h simulated night shift), and ending with 12 h at home. The key difference between the three conditions is the presence or absence of an intra-shift nap and the duration of that nap. Condition 1 will involve a simulated 12-h night shift with no nap: total sleep deprivation. Condition 2 will comprise another simulated 12-h night shift and a 30-min nap opportunity. Condition 3 will involve a simulated 12-h night shift and a 2-h nap opportunity. There will be a mandatory 1–3 week washout period between conditions. The order in which participants complete the study conditions will be balanced by a William’s square design. In the paragraphs below, we outline the details of our experimental study in accordance with the CONSORT/SPIRIT statement. Figure 1 illustrates the flow chart of our trial, and Fig. 2 illustrates the SPIRIT template for enrolment, intervention, and assessment. The University of Pittsburgh Institutional Review Board (IRB) approved this study {24}, and our protocol has been registered with ClinicalTrials.gov ({2a} registration number: NCT04469803; public release date: 9 July 2020). All subjects are required to provide written informed consent (see Additional file 1, which reports on all elements of the SPIRIT checklist). All elements of the World Health Organization Trial Registration Data Set can be found in this article, supplemental file, and the ClinicalTrials.gov registration.

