**Fig. 2 Fig2:**
[figure not shown]
Schedule of enrolment, interventions, and assessments. 0 = start of at-home phase. *t*_*1*_ = 12 h post allocation. *t*_*2*_ = 24 h post allocation. *t*_*3*_ = 36 h post allocation. *t*_*4*_ = 48 h post allocation. *t*_*5*_ = 60 h post allocation. *t*_*6*_ = 72 h post allocation

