### Intervention description {11a}

Our intervention of interest is intra-shift napping. All subjects in our study protocol will participate in two intervention nap conditions and one no-nap comparison condition. All nap opportunities will be available between 0200 and 0400 h during the in-laboratory phase and simulated night shift. We chose this time period given that (A) EMS call volume (workload) is often low or limited at this time, and many who are allowed to nap on duty may use this time period for sleep, and (B) this window of time coincides with a known time of high homeostatic sleep pressure and minimal circadian alerting signal [21]. Protocol conditions 2 and 3 will involve scheduled intra-shift nap opportunities of 30 min and 2 h, respectively. Our choice of 30 min and 2 h for the nap opportunities was based on the following: (A) previous research has suggested that short duration naps are optimal during night shift work for sustained or improved performance and avoidance of sleep inertia (that groggy feeling experienced upon waking) [8]; (B) shorter duration naps are attractive in public safety because EMS work is unpredictable and when called upon, an EMS worker must react quickly and make medical decisions to care for the acutely ill and injured; (C) many EMS employers who may not endorse sleeping while on duty might be amenable to short versus longer opportunities for intra-shift napping [51]; and (D) blood pressure and HRV are tightly tied to sleep and depth of sleep [9]. As described previously, normal dips in BP and parasympathetic-driven changes in HRV often occur when entering deeper, slow-wave sleep, which can occur 30 min or longer after beginning sleep [9, 53]. Therefore, the longer 2-h nap condition may be superior in terms of a cardiovascular-focused health benefit than would the shorter 30-min nap condition.

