Following the initial 36 h at home, the laboratory phase will begin with participants arriving at the lab between 1700 and 1800 h. The simulated night shift will begin at 1900 and end at 0700 (12 total hours) the next day. Participants will follow study intervention procedures based on the order in which they were randomized (i.e., condition 1 = no nap, condition 2 = brief nap opportunity of 30 min, or condition 3 = longer nap opportunity of 2 h). We have designed the simulated night shift to include activities that are common during real work conditions. In most EMS operations, the dispatch (or call) volume is often reduced during nighttime hours. Night shifts for EMS shift workers often involve long periods of downtime with limited and unpredictable patient-related activity. During downtime, EMS shift workers read, watch television, use the Internet, or complete continuing education, or sleep if permitted. For purposes of this study, we will allow participants to engage in these activities with the exception of sleeping. Participants will sleep only when approved to do so for the two napping conditions. Our simulated night shift will involve four diverse patient encounters introduced at random times throughout the simulated night shift (minus the set-aside times for the napping conditions). We will separate these encounters throughout the shift so that no two occur back to back within a short time period. We will also introduce these mock patient encounters at similar time intervals for all study participants so that the workload does not differ in a meaningful way. Four patient encounters during nighttime hours is a moderate level of workload. The four mock patient encounters will include a low acuity patient encounter (i.e., a lift assist), a high acuity patient encounter (i.e., a cardiac arrest), and two moderate acuity patient encounters (i.e., a traumatic injury and a patient with a medical emergency). Study staff will administer these mock patient encounters with simulated “alarms” sounding as if the participant was at work. We will allow for the movement of the participant (and mock patient) within the laboratory space and the office space where the laboratory is located. Patient treatment (e.g., cardiopulmonary resuscitation) will be performed on a low-fidelity manikin. Study staff will use standardized checklists to document the actions of study participants in accordance with state- and national-level protocols for EMS clinical care. The simulated patient encounters will not involve operating an ambulance or driving simulator.

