### Implementation {16c}

Two previous studies with a similar study design reported concealing the objectives of the study and providing study participants with limited details of the intervention until moments before the intervention was administered [56, 59–61]. These studies show that full blinding of study participants and concealment of intervention details is difficult. Our protocol faces similar challenges. For purposes of our study, once the opaque envelope with randomization assignment is opened, investigators, study staff, and participants will be alerted to the assigned napping condition. Given this design, our study is open-label.

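### The condition is disclosed at the start of each session, 7–9 h or up to about 43 h (the text does not settle which) before the conditions first differ at 0200

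*Protocol article*

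**What the plan says.** Concealment mechanism {16b} of the Protocol article puts the assignment in "sealed opaque envelopes to be opened at the beginning of each session". Implementation {16c} and Who will be blinded {17a} add that, once the envelope is open, participants, staff and investigators know the napping condition; only the primary analyst stays blinded.

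Trial design {8} says that every condition "will begin with a 36-h at-home period, followed by 24 total hours in the lab", with a final 12 h at home. Under Intervention description {11a}, arrival is at 1700–1800 and the shift runs from 1900 to 0700. On the nap the section states: "All nap opportunities will be available between 0200 and 0400 h". The same section has participants leave the laboratory at 1900 on the day the shift ends.

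The Fig. 2 legend gives "0 = start of at-home phase" and labels the next time point "12 h post allocation", with later points counted in the same way up to 72 h.

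Implementation {16c} also reports that two similar studies concealed their objectives, "providing study participants with limited details of the intervention until moments before the intervention was administered". It notes that full concealment is difficult and declares the trial open-label.

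**The concern.** Apart from the nap, the three conditions follow the same plan, and the nap cannot start before 0200. Knowledge of the condition after 0200 cannot be avoided. Knowledge before 0200 can, at least for participants.

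A participant who knows that a night without sleep is coming may rest differently beforehand, and staff may pace the early shift differently. Such behaviour would follow the condition, not the period, so the balanced ordering of conditions would not remove it. The hours concerned are also analysed. Under Outcomes {12}, SDNN is summarised over 24 h, and the BP dip is measured against daytime or waking readings, many of which are taken before 0200.

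**Working it through.** **Inputs.** Phases of 36 h at home, 24 h in the laboratory and 12 h at home (Trial design). Arrival 1700–1800, shift 1900–0700, nap window from 0200, departure 1900 (Intervention description). Daytime 0700–2259 and nighttime 2300–0659 (Outcomes).

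**The plan's own total.** 36 + 24 + 12 = 72 h, as stated.

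**Placing the clock.** The laboratory phase lasts 24 h and ends at 1900, so its nominal start is 1900. The home phase starts 36 h earlier, at 0700 on day 1. The nap window opens at 0200 on the night of the shift, 1900 + 7 h.

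**Lead time** = 0200 minus the time of opening:

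| Envelope opened at | Lead before 0200 |
|---|---|
| Start of the home phase (0700, day 1) | 36 + 7 = 43 h |
| Start of the home phase, if the 36 h end on arrival at 1800 or 1700 | 36 + 8 = 44 h or 36 + 9 = 45 h |
| Laboratory arrival (1800 or 1700) | 8 or 9 h |
| Start of shift (1900) | 7 h |

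**Which reading applies?**
- For the home phase: Fig. 2 sets zero at the start of that phase and counts from allocation. The assignment is made per visit, and Eligibility criteria {10} uses *visit* for the whole 72 h.
- For the laboratory: Sequence generation {16a} speaks of in-lab sessions, and Who will be blinded {17a} refers to people on site when the assignment is revealed.

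The laboratory reading is at least as well supported. The text does not decide between the two.

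**Analysed hours that are exposed.** Assume that 24-h blocks run from the start of monitoring at 0700, which matches the 24-h and 48-h marks in Fig. 2. The block that contains the shift then has 12 h at home and 12 h of shift.
- Opening at the start of the home phase: 19 of its 24 h (0700–0200, 79%) fall after disclosure and before divergence. They include all 16 daytime hours and 3 of the 8 nighttime hours (2300–0159). The whole preceding 24-h block also follows disclosure.
- Opening at arrival or at shift start: 7–9 of the 24 h (29–38%). These are 4–6 daytime hours (from 1900, 1800 or 1700 to 2259) and the same 3 nighttime hours.

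These are shares of time in which behaviour could differ. They do not measure bias.

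**What later opening can conceal.** Each participant meets each condition once. In session 1 any of three conditions is possible. In session 2 one is ruled out. In session 3 the condition is known by elimination. With balanced orders, one third of participants have the no-nap condition first and so know that session 2 includes a nap. Another third have it last, when it can be deduced.

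**The case against.** Several parts of the opposing case stand.

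- **The longer lead is not established.** A reader might infer from Fig. 2 that participants learn the condition about 43 h ahead. The documents do not support that as a fact. Allocation is not the same as opening the envelope: the consent section {26a} places randomization right after consent, so the figure's label cannot date disclosure. On the laboratory reading, sleeping extra at home because of the assignment is not possible, since the assignment is still sealed.
- **Safeguards exist.** In the laboratory, participants sleep only when permitted, and mock encounters come at similar intervals for everyone. Ratings and vigilance tests are hourly. At home there is a structured sleep and food protocol, with abstinence from exercise, caffeine, alcohol and nicotine. Actigraphy runs for the full 72 h and would record a home nap, though it would not prevent one. The outcomes are device-measured.
- **Staff need some notice.** Encounters are placed around the nap times, and Plans for assessment {18a} limits the sleep-staging device to the two nap conditions. It would go too far to say that nobody needs the assignment before 0200.
- **Participants expect a night without sleep.** The eligibility criteria require that commitment, so only its timing can be concealed.

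The open-label declaration does not answer the point. It concerns the difficulty of full blinding and gives no reason for disclosing hours before the nap, when the same section cites studies that disclosed later.

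**Conclusion.** The point holds as an avoidable weakness in when the condition is disclosed. On every reading, participants and staff know the condition hours before the conditions differ: about 7–9 h if the envelope is opened for the in-lab session, and up to about 43 h (44–45 h if the 36 h end on arrival) if it is opened when home monitoring starts. The exposed hours enter the 24-h SDNN and the daytime and waking BP reference. Their share of the shift block depends on the assumption that blocks run from 0700.

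A reader might go further and infer that the comparison between conditions is biased. The documents do not support that. They contain no evidence that behaviour changes with the assignment, the direction of any effect is uncertain, and no shift in SDNN or BP dip can be calculated from them. It is a risk, limited by the safeguards above, and it can be reduced cheaply.

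**What to change.** 1. In Concealment mechanism {16b}, state that the envelope is opened on site during the simulated shift, shortly before 0200 in every session, with just enough time to set up the nap and the sleep-staging device.
2. Keep 0200–0400 free of mock encounters in every condition, so that procedures before the envelope is opened are identical. This also serves the protocol's aim of equal workload.
3. Relabel the Fig. 2 times as hours from start of monitoring.

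The cost is about a sentence in each place and an instruction to the night staff, with no added personnel or outcome measurements. Staff must be ready for any of the conditions until the envelope is opened. The gain is also partial: concealment is full in session 1, incomplete in session 2 because one condition is ruled out, and absent in session 3.

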### Implementation {16c}

Two previous studies with a similar study design reported concealing the objectives of the study and providing study participants with limited details of the intervention until moments before the intervention was administered [56, 59–61]. These studies show that full blinding of study participants and concealment of intervention details is difficult. Our protocol faces similar challenges. For purposes of our study, once the opaque envelope with randomization assignment is opened, investigators, study staff, and participants will be alerted to the assigned napping condition. Given this design, our study is open-label.

### Assignment of interventions: blinding

#### Who will be blinded {17a}

One member of the study team, the primary data analyst (statistician), will be blinded for the duration of the study. All other study investigators, staff, and participants will be blinded to the condition assignment immediately prior to each session. Once the envelope is opened, all who are on site at the time of randomization will be made aware of the assignment and unblinded.

#### Procedure for unblinding if needed {17b}

N/A. There are no procedures for unblinding once the opaque envelope has been opened.

### Data collection and management

#### Plans for assessment and collection of outcomes {18a}

The protocol for measurement assessment and collection of outcome measures includes the use of continuous monitoring devices, such as ABPM for serial BP measurement, and cardiac Holter monitoring for serial HRV measurement for the 72-h protocol repeated three times for each study participant. For ABPM, we will assess BP hourly with the Oscar2 device manufactured by SunTech Medical (Morrisville, NC, USA). For HRV, we will use the NASIFF CardioCard® 5-lead, 3-channel device (NASIFF Associates, Inc., Central Square, NY, USA). As described in the “Outcomes {12}” section, we will administer surveys at baseline and again at pre-specified time points in order to capture subjective ratings of sleep and fatigue. Our plan for assessment will also include monitoring of sleep depth during the conditions that involve intra-shift napping. We will use the Zmachine® Synergy for purposes of assessing depth of sleep during the in-laboratory phase only and only during the two napping conditions. Sleep versus wake will be assessed with a wrist-worn actigraphy device (wGT3X-BT by Actigraph Corp., Pensacolo, FL, USA) worn continuously during the three 72-h protocols.

Participants will complete standardized surveys at baseline, throughout the study protocol, and at the end of each 72-h period. At baseline, participants will be asked to complete a standard demographic questionnaire, the PSQI, ESS, CFQ, OFER, CBI, and SAS surveys. Study staff will complete seven standardized, paper-based data collection forms. These forms document the following: (A) the time when devices (i.e., wrist actigraphy, ABPM, Holter monitors) are applied and/or removed; (B) results of calibration of continuous monitoring devices (i.e., ABPM, Holter monitor, wrist actigraphy, and the Zmachine® Synergy). Calibration of the Oscar2 device will be similar to the process described in a separate publication [35]; (C) in-laboratory hourly, self-reported, single-item assessments of fatigue, sleepiness, irritability, stress, and related constructs analogous to the items used in previous research [92]; (D) in-laboratory, hourly measurements of psychomotor vigilance with the brief psychomotor vigilance test (PVT-B). The PVT-B is widely used to assess reaction time (vigilance and alertness), shown to be reliable, is sensitive to changes in sleep and sleep deprivation, resistant to practice effects, and considered a valid assessment of neurocognitive performance [93–96]; and (E) self-reported, single-item assessments of fatigue, sleepiness, irritability, stress, and related constructs [92] immediately upon waking from in-laboratory napping periods; again at 10 min, at 20 min, and at 30 min after waking from a nap. We will also document vigilance with the PVT-B immediately upon waking, at 10 min, 20 min, and 30 min. Study staff will transcribe the data documented on paper-based forms into a REDCap database immediately after a form is completed. A second study staff member will review the transcription for accuracy and completeness.

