
For conditions 2 and 3, the nap opportunities will be introduced between 0200 and 0400. In addition to wearing wrist actigraphy for sleep/wake monitoring, all participants will wear the portable Zmachine® Synergy machine provided by the General Sleep Corporation (Cleveland, OH). The Zmachine® Synergy is a non-invasive sleep staging device that produces numerous measures to quantify and differentiate light sleep (stages 1 and 2) from deeper sleep (stages 3 and 4) from rapid eye movement (REM) sleep. The Zmachine® Synergy will be used only when the participant is engaging in his/her sleep opportunity from 0200 to 0400 and during the recovery period of sleep. With these data, we will explore the association between stages of sleep (depth of sleep) and changes in BP and HRV during intra-shift napping/sleep.

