### Outcomes {12}

Our primary outcomes of interest include blunted BP dipping and reduced HRV as measured by the standard deviation of the inter-beat intervals of normal sinus beats (SDNN). Blunted BP dipping will be calculated using two measures. First, we will quantify sleep vs. wake BP dipping by identifying the participant’s sleep and wake times and stratifying the hourly ABPM measures into sleep vs. wake measures. The ratio of sleep-to-wake BP is calculated by taking the difference between the mean systolic and diastolic BP during the sleeping hours and the mean systolic and diastolic BP during waking hours. We define dipping status as follows: (mean wake hours BP − mean sleep BP divided by mean wake hours BP) × 100. Non-dipping status will be defined as sleep hours BP dip of less than 10%, assessed with systolic BP (SBP) and diastolic BP (DBP) [22, 69]. Next, we will stratify each 24-h period into nighttime vs. daytime periods and calculate nighttime BP dipping with the “wide fixed time method” [70, 71]. Daytime hours are defined as 0700 to 2259 h, and nighttime hours are defined as 2300 to 0659 h [70, 71]. The ratio of night-to-day BP is determined by taking the difference between the mean systolic and diastolic BP during the nighttime hours (2300 to 0659 h) and the mean systolic and diastolic BP during daylight hours (0700 to 2259 h). For this method, nighttime dipping status is determined as follows: ((mean daylight BP − mean nighttime BP) ÷ mean daylight hours BP) × 100. We will assess dipping vs. non-dipping status during sleep hours and during nighttime hours for all periods of observation and for all study conditions.

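### Hourly blood pressure readings are further apart than the 30-min nap is long, so half or more of short naps may contain no sleep reading

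*Protocol article*

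**What the plan says.** The section Plans for assessment and collection of outcomes {18a} sets the cadence: "For ABPM, we will assess BP hourly". Outcomes {12} defines blunted dipping by two measures. The first is built by "stratifying the hourly ABPM measures into sleep vs. wake measures", and a dip below 10% counts as non-dipping. The second compares fixed clock windows: "nighttime hours are defined as 2300 to 0659 h", against daytime from 0700 to 2259.

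Intervention description {11a} gives the nap lengths: "Protocol conditions 2 and 3 will involve scheduled intra-shift nap opportunities of 30 min and 2 h, respectively". On timing it says only that "All nap opportunities will be available between 0200 and 0400 h".

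The explanation for the choice of comparators {6b} asks whether workers achieve a healthy dip during shorter as well as longer naps. Outcomes {12} also asks whether more deep sleep in an intra-shift nap goes with a deeper dip, and Statistical methods {20a} plans models that use the time spent in each sleep stage. The missing-data section {20c} calls a participant incomplete when fewer than 70% of scheduled BP readings are captured.

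**The concern.** The measurement interval (60 min) is twice the length of the shorter intervention (30 min), and actual sleep is shorter still by the time taken to fall asleep. A dip that occurs only while the participant is asleep is seen only if a reading happens to fall in that interval. The article does not state denser, triggered or aligned readings for naps.

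Three things are exposed: the contribution of the intra-shift nap to the sleep-versus-wake dip, the comparison of the two nap lengths on that measure, and the sleep-stage analysis, which needs BP values recorded inside the nap. The loss also differs by condition, because the 30-min nap loses readings far more often than the 2-h nap. The 70% rule does not catch it, because it counts all scheduled readings: a participant with no nap reading can still be classed as complete. Readings that were never taken cannot be recovered in the analysis.

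**Working it through.** **Inputs from the protocol article.** Reading interval 60 min; nap opportunities 30 and 120 min within 0200 to 0400; 25 participants, 5 mmHg difference in mean dip, within-participant standard deviation (SD) 6 mmHg, two-sided alpha 0.05, stated power 80%.

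**Assumptions.** Actual sleep of 20 to 30 min in the short nap and 60 to 120 min in the long one; the hourly clock is random relative to sleep onset.

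**1. The plan's own figure.** Paired t test, SD of the difference = 6 × √2 = 8.49 mmHg, noncentrality = 5 / 8.49 × √25 = 2.95. Power is 80.7%, which reproduces the stated 80%.

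**2. Readings inside a nap.** A sleep interval of L minutes on a 60-min grid with random phase contains floor(L/60) readings, plus one more with probability (L mod 60)/60.

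| Minutes asleep | 0 readings | 1 reading | 2 readings |
|---|---|---|---|
| 20 | 67% | 33% | 0% |
| 30 | 50% | 50% | 0% |
| 60 | 0% | 100% | 0% |
| 90 | 0% | 50% | 50% |
| 110 | 0% | 17% | 83% |
| 120 | 0% | 0% | 100% |

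A simulation gave the same shares. These are scheduled readings. If each were valid with probability 0.70 (an assumption), the share of short naps with no valid reading would be 1 − 0.50 × 0.70 = 65% for 30 min asleep and 1 − 0.33 × 0.70 = 77% for 20 min.

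**3. Participants with a short-nap value.** 25 × 0.33 = 8.3 and 25 × 0.50 = 12.5, so about 8 to 12 of 25.

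**4. Power on those pairs (illustration).** The no-nap condition has no intra-shift sleep, so a nap dip can be compared only between the 30-min and 2-h conditions. With the same 5 mmHg and SD of the difference 8.49 mmHg, paired-t power is 30% with 8 pairs, 38% with 10 and 46% with 12.

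**5. The other BP measure.** The window from 2300 to 0659 holds about 8 hourly readings and the daytime window about 16, in every condition.

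**The case against.** The strongest reply is that only part of the outcome set is affected. The fixed-window night dip has about eight readings per night whether or not anyone naps, and heart rate variability comes from a continuous Holter recording. The stated aim covers dipping during sleep and during nighttime hours, and the power statement refers to mean BP dip without restricting it to the nap. All of this stands. A reader might infer that the trial cannot assess BP dipping, or that its 80% power is lost; the documents do not support either.

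The fixed-window measure does not replace nap readings, however. With an assumed waking level of 120 mmHg, a 10% to 20% dip is 12 to 24 mmHg. Lasting 30 min, it moves an 8-h mean by 12 × 0.5/8 = 0.75 to 24 × 0.5/8 = 1.5 mmHg. Pooling sleep over a longer period would add readings from the 1300 to 1500 recovery nap and from sleep at home, but these do not measure the intra-shift nap.

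A reader might also infer that the 30-min condition has no sleep readings at all. That needs both readings and nap onset to fall exactly on the hour, and the article states neither. Nor are all nap dips missing or based on one value: a fully slept 2-h nap gives two readings.

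Finally, one might try to size the extra noise of a single reading. With all 25 pairs and an assumed SD of 8, 10 or 12 mmHg for both nap dips, power is 56%, 40% or 29%. If only the short-nap value is noisier and the other stays at 6 mmHg, it is 67%, 54% or 43%. The article gives no basis for these SDs, and whether its 6 mmHg already reflects sparse nap readings cannot be checked. The sleep-stage analysis is described as exploratory, which lowers the stakes there.

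**Conclusion.** The point holds within limits. Followed as written, the hourly schedule leaves 50% to 67% of 30-min naps without a sleep reading and the rest with one, assuming 20 to 30 min asleep and random alignment. A 2-h nap with 60 to 120 min asleep has one or two. This undermines the intra-shift nap part of one of the two primary dipping measures, the comparison of nap lengths on that measure, and the exploratory sleep-stage work.

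The power figure of about 30% to 46% is an illustration for a contrast that the article does not specifically power. It assumes 8 to 12 usable pairs and the planned SD. The effect of single-reading noise cannot be sized from the document.

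**What to change.** Set a fixed clock time, within the stated window, for the 30-min nap. Offset the hourly schedule so that one reading falls about 20 min after lights-out, and keep the same reading times in all three conditions, including no-nap. This needs only device programming and a fixed nap time, and it adds no cuff inflations. A participant may still be awake at that reading; the sleep-staging record will show this.

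If a few extra readings are wanted from 0200 to 0400 and from 1300 to 1500, take them in all conditions. For the fixed-window night dip, use only the hourly readings or time-weighted means. Otherwise the nap window dominates: reading every 10 to 15 min would put 8 to 12 readings there against 6 in the rest of the night, so 8/14 = 57% to 12/18 = 67% of the night readings instead of 2/8 = 25%. The cost of extra readings is possible sleep disturbance from cuff inflation. Either change must be in place before data collection.
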